### Toward predictive medicine

Precision medicine is an innovative approach to tailoring disease treatment that takes into account differences in genetics, environment, and lifestyle of people. The goal of precision medicine is to target treatments to patients who are most likely to benefit from them. Due to the specific problems of HNSCC (radioresistance, high risk of recurrence and secondary cancer, toxicity of treatments), it appears interesting to be able to predict response to conventional treatments using models mimicking the original patient’s tumor. Such models could also be used to test new therapy combinations or new compounds in order to predict their clinical effectiveness and/or the identification of predictive molecular signatures.

Functional assays in precision oncology are based on direct exposure of cancer tissues derived from affected individuals to drugs to predict clinical response. These functional approaches allow to evaluate the response to treatments by considering all the intrinsic characteristics of the tumor without prior molecular analysis. The results can then be correlated to different biological parameters (DNA, mRNA, non-coding RNA, proteins, etc. from various origins like tumor or blood for example) in order to identify predictive biomarkers of treatment response. Functional assays can be performed using various cancer models [6], including Patient-Derived Tumor Organoids (PDTO) which represent an emerging pre-clinical model at the interface of cell lines and patient-derived xenografts mouse models.

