### Study objectives

The main objective of the study is to assess the feasibility of using PDTO from HNSCC as tools for predicting response to treatments.

The secondary objectives are: i) to assess the feasibility of in vitro functional assays for evaluation of sensitivity to treatments (chemotherapy, radiotherapy, PARP inhibitors and immunotherapy); ii) to investigate the predictive value of PDTO for conventional chemotherapy and radiotherapy; iii) to evaluate the PARP inhibitor-mediated sensitization of radiotherapy; iv) to assess the ability of PDTO to repair DNA lesions by homologous recombination [(HRD (Homologous Recombination Deficiency)/HRI (Homologous Recombination Intermediate)/HRP (Homologous Recombination Proficiency) status); v) to identify molecular signatures for prediction of response (of PDTO and patients) to treatments.

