#### Medical data collection

Medical data collected for each patient in order to correlate biological data (including PDTO response to treatment) with clinical response are indicated in Table 2.

**Table 2 Tab2:** Medical data collected for each patient

Clinical parameters	Age, sex, weight, height, ECOG performance status, Exposure to tobacco and alcohol, Cancer location and TNM-8 classification
Histological diagnosis	Type, squamous differentiation, keratinization type, p16 status
Biologic parameters	Serum neutrophils, albumin and leukocytes levels
Pathological pronostic factors	Surgical margin, lymph node metastasis with or without capsular rupture, vascular or lymphatic embolization, perineural invasion
Oncologic treatments	Radiotherapy (volume, dose, fraction) Chemotherapy (molecules, administration regimen)
Response to treatment	Disease-free survival, Progression-free survival, Overall survival.

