##### Targeted sequencing by NGS

“Mutational status (SNV, indels, CNV and translocations)” will be established on original tumor samples and PDTO derived from the primary tumor by targeted re-sequencing of a panel of 580 genes involved in cancer for DNA and of a panel of 57 genes implicated in protein fusion for RNA. DNA and RNA from samples will be extracted using QIAamp DNA kit (Qiagen) and NucleoSpin miRNA kit (Macherey Nagel, Hoerdt) respectively. DNA and RNA libraries sample preps and targeted enrichment will be performed using SureSelect XT HS2 DNA Reagent Kit (Agilent) and SureSelect XT HS2 RNA Reagent Kit (Agilent) respectively according to manufacturer’s instructions. Paired-end sequencing will be realized on a Nextseq500 sequencer from Illumina with a mean depth of coverage of 1000X. Bioinformatic analysis will be performed using an already developed pipeline. Briefly, duplicate reads merge, using unique molecular identifier, will be based on AGeNT (Agilent). The alignments will be based on BWA and GATK for BAM recalibration. Variant calling will be performed using Haplotype caller, Lofreq and OutLyzer. Finally, variant annotation will be realized with Alamut Batch and Annovar. The evaluation of copy number of targeted genes (Gain or Loss) will be evaluated using already published softwares such as ONCOCNV, CNVkit or current relevant tools.

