#### Statistical analyses

Qualitative variables will be described using the sample numbers and percentages. Quantitative variables will be described using the mean (+/− standard deviation) or the median and the range if normality hypothesis is not verified*.*

To address the primary objective, the rate of successful PDTO establishment, i.e., the rate of tumor samples usable for predictive functional assays based on PDTO, will be estimated with its 95% confidence interval. Then, PDTO response to treatment will be correlated with the clinical response by performing a Chi2 test and computing the Cohen’s kappa coefficient. Associations between biological parameters and clinical response will be assessed by one-way analysis of variance (or the non-parametric Kruskal-Wallis test, if necessary). Receiver Operating Characteristic (ROC) curves and a logistic regression model will also be used to identify predictive factors of clinical response.

An alpha level of 5% will be considered to indicate statistical significance for each statistical analysis and confidence interval.

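### The unadjusted 5% level set for every analysis gives no error control for the molecular search in secondary objective v

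*Protocol article*

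**What the plan says.** The error-rate rule is in the protocol article, Statistical analyses: "An alpha level of 5% will be considered to indicate statistical significance for each statistical analysis and confidence interval". No multiplicity adjustment, false discovery rate or validation step is named anywhere in the article.

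The same section gives the tests against clinical response. "Associations between biological parameters and clinical response will be assessed by one-way analysis of variance", with Kruskal-Wallis as the alternative. Then "Receiver Operating Characteristic (ROC) curves and a logistic regression model will also be used to identify predictive factors of clinical response". The parameters and candidate factors are neither listed nor counted.

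Secondary objective v, in Study objectives, is "to identify molecular signatures for prediction of response (of PDTO and patients) to treatments". The data that can feed it are described under the laboratory methods:

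- Targeted sequencing by NGS: "targeted re-sequencing of a panel of 580 genes involved in cancer for DNA", plus a 57-gene RNA fusion panel.
- Transcriptomic analysis: mRNA and lncRNA profiling, analysed with DESeq2. No contrast or error rate is stated.
- Copy number variations analysis: low-pass whole-genome sequencing.

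The clinical outcomes named under Evaluation of response to treatments are PFS, DFS and OS.

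**The concern.** A 5% level per test limits the error of a single prespecified test. It does not limit the number or the proportion of false findings when hundreds of features are tested against the same outcome. Read literally, the rule allows each panel gene with p below 0.05 to be reported as a predictive factor.

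This is more than silence that an analysis plan could fill. The article states the level for each analysis, so a plan that added false discovery rate control would depart from it. The Discussion presents the signatures as a step towards choosing treatments for individual patients, so chance findings could be carried into later work as candidate biomarkers. A related problem arises if ROC curves and logistic regression are used to pick factors and then judged on the same patients: the apparent AUC of the chosen factor is too high.

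**Working it through.** **1. Sample base.** Sample size determination asks for 89 assessable tumors (98 patients) for a 95% interval 20 points wide at a rate of 60%. The Wilson interval reproduces this: width 0.1995 at n = 89 and 0.2006 at n = 88. Inflation: 89 × 1.1 = 97.9, so 98. Established lines: 0.6 × 89 = 53.4, about 53. Original tumors are sequenced too, so tumor-marker analyses could use 89. I therefore take N = 53 and N = 89.

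**2. Chance findings with no true association** (number of tests × 0.05, per outcome):

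- 580 genes: 580 × 0.05 = 29
- 580 + 57 = 637 genes: 637 × 0.05 = 31.9
- Chance of at least one, if independent: 1 − 0.95^57 = 94.6% for the fusion panel alone, and about 100% for 580.

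**3. Allowance for rare alterations.** Mutation status is mostly altered or not altered. With few altered patients the test cannot use its full 5%. Expected chance findings among 580 independent null genes, using Kruskal-Wallis on binary status and response groups of nearly equal size:

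| Assumed alteration frequency | 2% | 5% | 10% | 20% |
|---|---|---|---|---|
| n = 35 (18 with the event) | 0.3 | 5 | 19 | 30 |
| n = 89 (45 with the event) | 6 | 26 | 30 | 29 |

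So 29 to 32 is close to a ceiling. At n = 35 a gene altered in three or fewer patients can never reach p < 0.05. The n = 35 is an assumption: about two thirds of 53, since the Background says that more than two thirds of operated patients have adjuvant treatment. The event counts are also assumptions.

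**4. Share of declared markers that are false.** With π the share of features truly associated:

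false share = 0.05(1 − π) / [0.05(1 − π) + π × power]

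Power is for a two-sided comparison of two equal groups, Φ(d√(N/4) − 1.96), where d is the standardized effect. Example, N = 89, d = 0.5: 0.5 × √22.25 − 1.96 = 0.40, so power is 0.655. At π = 1% the false share is 0.0495 / (0.0495 + 0.00655) = 88%.

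| N, d | π = 1% | π = 5% | π = 10% |
|---|---|---|---|
| 53, 0.5 | 92% | 68% | 50% |
| 53, 0.8 | 86% | 53% | 35% |
| 89, 0.5 | 88% | 59% | 41% |
| 89, 0.8 | 84% | 50% | 32% |

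False findings are the majority when π < 0.05 / (0.05 + power): below 4.8% at full power, 5.9% at 80% and 9.1% at 50%.

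**5. Apparent AUC after selection.** In simulation with continuous pure-noise markers, and direction chosen from the data, the best of 580 has a mean apparent AUC of about 0.81 at n = 35, 0.76 at n = 53 (27 events) and 0.70 at n = 89. The true value is 0.50. Binary markers with rare alterations give lower figures.

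**The case against.** The strongest objection is that the article never says how many features are tested against clinical response. The Medical data collection table uses almost the same label for three blood measures only: "Serum neutrophils, albumin and leukocytes levels". ANOVA suits such quantitative variables better than mutation status. The section on transcriptome and CNV analysis describes PCA, clustering and pathway plots comparing PDTO with tumor, not tests against outcome. This stands as an ambiguity, but the narrow reading would leave objective v with no stated test against patient response. The Background section Toward predictive medicine speaks of assay results being "correlated to different biological parameters (DNA, mRNA, non-coding RNA, proteins, etc. from various origins", with the aim of finding predictive biomarkers. The wide reading is the one that makes the plan coherent.

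Second, false discovery rates and internal validation are often left to an analysis plan, and this is a condensed article on a feasibility study. That holds for the AUC correction, which I treat as an add-on. It does not hold for the 5% sentence, which is an explicit rule.

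Third, a reader might infer that thousands of features are screened at 5%, with about 1,000 chance findings from the transcriptome. The documents do not support this. That count needs an assumed 20,000 transcripts (20,000 × 0.05), and DESeq2 may already adjust its p-values.

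**Conclusion.** The concern holds in a limited form. The 5% rule per analysis gives no error control for the molecular search in objective v. On the wide reading of biological parameters, up to about 29 to 32 of the 637 panel genes would be declared per outcome by chance if nothing were associated, and fewer where alterations are rare. If some features are truly associated, an estimated 32% to 92% of declared markers could be false.

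A reader might go further and infer that the signatures will be dominated by false positives. That does not follow: the false share is a majority in some of the scenarios above and about a third in the most favorable. It rests on effect size, sample size and share of true features, none of which the article gives for this search. Nor can a single AUC inflation be quoted for the gene panel: the 0.70 to 0.81 range is for continuous noise markers at assumed sample sizes.

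The primary objective is a rate with its confidence interval and is not touched.

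**What to change.** Replace the blanket sentence with three statements:

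1. The unadjusted 5% level applies to the primary establishment-rate interval and to one named test of PDTO response against clinical response.
2. Molecular screens against response use Benjamini-Hochberg false discovery rate control at 5% within each platform and outcome, and are labelled exploratory. The text should list which features count as biological parameters and say whether the DESeq2 results are already adjusted.
3. Where ROC curves or logistic regression select factors, AUCs are corrected by bootstrap or cross-validation that repeats the selection step.

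No new patients or assays are needed. The cost is fewer declared markers and lower AUCs. Under Benjamini-Hochberg at 5%, as the true share goes from 1% to 10%, power per truly associated feature at effect 0.8 is about 15% to 45% with N = 53 and 56% to 82% with N = 89. At effect 0.5 it is below 2% with N = 53 and 2% to 17% with N = 89. The study can therefore confirm only strong signals, and the text should say so.

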### Data management

Medical data management will be performed by an independent data management center. The data collection will be done using an eCRF (electronic Case Report Form) and in accordance with the study protocol. After checking accuracy and completeness of the recorded data, the eCRFs will be signed by the investigator and archived by the data management center.

## Discussion

PDTO are preclinical models that mimic morphological and genetic characteristics of their original tumors [8]. Recent studies on various tumor types such as colorectal and urogenital cancers appear to show a correlation between the response of PDTO to treatment and the clinical response of patients [7]*.* These results are promising but not well studied in HNSCC.

We propose to perform this clinical study to compare the response to treatment of PDTO in HNSCC and the clinical response of the patients from whom they are derived. Our aim is both to demonstrate the interest of PDTO as predictive tools for each patient in view of a personalized medicine, and to use the established HNSCC tumor organoids collection for preclinical evaluation of new therapeutic compounds/strategies as well as for the identification of predictive molecular signatures. Eventually, PDTO could allow a better selection of treatments to which the tumors would be most sensitive and to limit the sequelae related to potentially less effective treatments, thus finding their place in true precision oncology protocols.

## Data Availability

Not applicable.

## Abbreviations

APTC: Antigen Presenting Tumor Cells
CNV: Copy Number Variation
CGH: Comparative Genomic Hybridization
DFS: Disease Free Survival
eCRF: electronic Case Report Form
FBS: Fetal Bovine Serum
ENT: Ear Nose and Throat
FDA: Food and Drug Administration
HNSCC: Head and Neck Squamous Cell Carcinomas
HR: Homologous Recombination Deficiency
HRI: Homologous Recombination Intermediate
HRP: Homologous Recombination Proficiency
NGS: Next Generation Sequencing
OS: Overall Survival
PARP: poly-ADP-ribose-polymerase
PBMC: Peripheral Blood Mononuclear Cells
PCR: Polymerase Chain Reaction
PD1: Programmed death-1
PDTO: Patient-Derived Tumor Organoids
PFS: Progression Free Survival
ROC: Receiver Operating Characteristic
UMIs: Unique Molecular Identifiers
